### 2.13. Statistical Analysis

Continuous variables will be presented as means and standard deviations, while categorical variables will be presented as frequencies (%) and percentiles. The homogeneity of the demographic characteristics and baseline variables between the two groups will be evaluated to choose the appropriate analysis methods. The independent t-test or Mann–Whitney U-test will be used for analysis, depending on the normality of data distribution. If there were significant between-group differences in baseline variables or demographic characteristics, regression analysis with covariates (analysis of covariance) will be conducted. The primary and secondary outcome measures will be analyzed in the same manner. We will also examine the consistency between objective and subjective sleep-related data obtained from actigraphy and patient-reported questionnaires.

Additionally, we will analyze the changes in sleep parameters assessed using polysomnography and sleep-related hormones before and after treatment in participants who underwent polysomnography. Both the full analysis set (FAS) and per-protocol analyses will be conducted. The FAS is the primary analysis of effectiveness and safety. It will include all participants initially assigned to each group, except those who did not meet the eligibility criteria, those who had not received any intervention, or those who had not completed any outcome measurements. The per-protocol analysis will include participants who have completed more than seven sessions. All statistical analyses will be performed by an independent statistical expert blinded to the allocation and procedure using SPSS version 25 (IBM, Chicago, IL, USA). Statistical significance is set at *p* < 0.05.

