### 2.3. Sample Size

In this trial, the ratio of the pharmacopuncture group to the acupuncture group will be 2:1 in order to obtain data on the side effects (safety) of the pharmacopuncture while securing statistical power [38,39]. The sample size of this study was determined based on the study by Xian et al. [40]. The mean differences in PSQI scores before and after treatment in the experimental and control groups were estimated to be 6.9 (standard deviation = 2.51) and 4.93 (standard deviation = 2.70), respectively. Based on this, the effect size calculated using G Power software, version 3.1.9.4 (Franz Faul, Christian-Albrechts-Universittt Kiel, Kiel, Germany) was 0.92. The number of participants required is then 74 for the experimental group and 37 for the control group, given a 2:1 allocation ratio, two-sided significance level of 0.05, and 95% statistical power. Considering a dropout rate of 20%, the total sample size of the experimental and control groups will be 92 and 46, respectively.

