### 2.9. Outcome Measures

#### 2.9.1. Primary Outcome

The primary outcome measure will be the mean difference in the total Pittsburgh Sleep Quality Index (PSQI) scores pre- and post-intervention (between visits 1 and 11) between the two groups. The PSQI is the most commonly used self-report questionnaire to assess sleep quality and disturbances over the past month. It comprises 19 self-rated items and evaluates seven components: subjective sleep quality, sleep latency, sleep duration, habitual sleep efficiency, sleep disturbances, use of sleep medication, and daytime dysfunction. The total PSQI score ranges from 0 to 21, with higher scores indicating poorer sleep quality [44]. The PSQI score will be assessed at baseline, visit 6, post-intervention, and follow-up visits.

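### Section 2.13 lets baseline significance tests and a normality check choose the primary analysis; one pre-named ANCOVA would be better, though the average cost is modest

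*Protocol article*

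**What the plan says.** Section 2.9.1 defines the primary outcome as the "mean difference in the total Pittsburgh Sleep Quality Index (PSQI) scores pre- and post-intervention (between visits 1 and 11") compared between the two groups. It is a difference in mean change.

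Section 2.13 then sets the analysis in three steps. Baseline homogeneity is assessed in order to select the method. The test is left open: "The independent t-test or Mann–Whitney U-test will be used for analysis, depending on the normality of data distribution". Adjustment depends on a result: "If there were significant between-group differences in baseline variables or demographic characteristics, regression analysis with covariates (analysis of covariance) will be conducted". The rule reaches the primary outcome, because "The primary and secondary outcome measures will be analyzed in the same manner".

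The section does not say which baseline variables are tested, which covariates enter once the trigger fires, or what happens if the data are both non-normal and imbalanced. Section 2.6 stratifies the randomisation by research institution, but institution does not appear in the analysis. Table 1 schedules the PSQI at visit 1, so a baseline value is planned for everyone.

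**The concern.** Three analyses of the same endpoint are possible (t-test on change, Mann–Whitney, ANCOVA), and preliminary tests on trial data decide between them. There are two objections of principle.

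- In a randomised trial a significant baseline difference is a chance event. Its p-value does not show whether the variable predicts the outcome, and that is the reason to adjust. Baseline PSQI is a component of the change score and the obvious covariate, whether or not the arms differ significantly on it.
- The Mann–Whitney branch compares ranks. If it is chosen, the result is no longer the mean difference defined in section 2.9.1.

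At stake are some precision, a correct estimate in trials with moderate baseline imbalance, and an effect measure that is known before the data are seen.

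**Working it through.** **Inputs from section 2.3.** Mean changes "were estimated to be 6.9 (standard deviation = 2.51) and 4.93 (standard deviation = 2.70), respectively"; design "given a 2:1 allocation ratio, two-sided significance level of 0.05, and 95% statistical power"; "The number of participants required is then 74 for the experimental group and 37 for the control group".

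**The plan's own figure.** Difference = 6.9 − 4.93 = 1.97. Pooled SD = √((2.51² + 2.70²)/2) = 2.607. Standardised effect = 1.97/2.607 = 0.756. Controls needed for a t-test: (1.960 + 1.645)² × 1.5 / 0.756² ≈ 34.1, so 35 and 70. With the Mann–Whitney efficiency 3/π = 0.955, 35/0.955 = 36.6, so 37 and 74, as stated. The stated size therefore follows from the means and SDs. (The printed effect size of 0.92 does not; that is a separate matter.) With 74 and 37 the change-score t-test has 96.1% power.

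**Assumptions not in the document.** The correlation r between baseline and visit 11 PSQI is taken as 0.3, 0.5 and 0.7. SDs are equal at the two visits. ANCOVA is triggered by baseline PSQI alone at p < 0.05.

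**Precision.** ANCOVA variance / change-score variance = (1 + r)/2 = 0.65, 0.75, 0.85. The change-score variance is therefore 1.54, 1.33 and 1.18 times the ANCOVA variance.

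**Simulation of the two-stage rule** (74 and 37, change SD 2.607, 160,000 trials per scenario):

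| | r = 0.3 | r = 0.5 | r = 0.7 |
|---|---|---|---|
| Power at 1.97, rule | 96.8% | 96.6% | 96.4% |
| Power at 1.97, ANCOVA always | 99.6% | 99.0% | 98.0% |
| Overall type I error, rule | 4.1% | 4.4% | 4.6% |
| Type I error given baseline p 0.05–0.20, rule | 10.2% | 8.9% | 7.4% |
| The same, ANCOVA | 5.2% | 5.0% | 4.9% |

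**Conditional shift.** For a baseline imbalance D, the change-score difference is off by (1 − r)D.
- A baseline p-value of 0.05 to 0.20 occurs in 15% of randomised trials (0.20 − 0.05). The mean |z| in that band is (0.1755 − 0.0584)/0.075 = 1.56.
- The baseline SD is 2.607/√(2(1 − r)) = 2.20, 2.61, 3.37. The factor √(1/74 + 1/37) is 0.2013.
- So D ≈ 1.56 × 0.2013 × SD = 0.69, 0.82, 1.06, and (1 − r)D ≈ 0.48, 0.41, 0.32 PSQI points. The simulation agrees, and the ANCOVA shift in the same trials is about 0.
- If the imbalance runs against the experimental arm (lower baseline PSQI there), power of the change-score test falls to about 85%, 87% and 90%.

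**Sensitivity to the SD assumption.** If the post-treatment SD is k times the baseline SD, the variance ratio is k²(1 − r²)/(1 + k² − 2rk). For k = 1.3 this is 0.81, 0.91 and 0.99. At r = 0.7 both approaches then have about 96% power, and the conditional type I error of the rule is close to 5%.

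**Normality step.** A simulated Shapiro–Wilk choice between t-test and Mann–Whitney (6,000 trials per scenario, normal and skewed data) rejects 5.7% under the null, against 5.5 to 5.6% for the t-test alone. Power changes by less than 2 points.

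**Other triggers.** If 10 independent baseline variables were tested, at least one would be significant in 1 − 0.95¹⁰ = 40% of trials; with 20, 64%. The number tested is not given and the sleep and quality-of-life scales are correlated, so these figures are illustrative only.

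**The case against.** The strongest defence is that the rule does little harm on average. Overall type I error stays at or below 5%, and power at the design difference exceeds the planned 95%. That stands, and it rules out several stronger readings.

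- A reader might infer that choosing a test from the data inflates the false-positive rate. For the rule as simulated it does not; the excess appears only conditionally on a moderate imbalance.
- A reader might infer that the trial is left badly short of power. That needs a smaller true effect than the one planned. At 1.3 points, for example, power would be about 0.70 against 0.76 to 0.86, but no such difference appears in the protocol.
- A reader might say that imbalance goes uncorrected. A change score subtracts baseline in full, so the fault is over-correction. The plan also adjusts when the difference is significant.
- A reader might say that the estimand is wholly open. In a linear model of a randomised trial, adjusted and unadjusted mean differences target the same quantity. Only the Mann–Whitney branch changes the effect measure.

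It is also fair that the precision gain rests on an unknown correlation and SD ratio, and that simulating baseline PSQI as the only trigger simplifies a rule under which any baseline or demographic variable can fire.

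The argument that details belong in a separate analysis plan does not succeed here. Section 2.13 states a rule: an analysis plan that follows it inherits the fault, and one that fixes a single model would contradict it.

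**Conclusion.** The point holds as a should-fix. The protocol fixes the primary analysis by a data-dependent rule that has no inferential basis under randomisation and, in one branch, departs from the outcome defined in section 2.9.1.

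At the planned effect the rule gives up about 1.6 to 2.8 percentage points of power relative to ANCOVA always, under equal SDs and r from 0.3 to 0.7. In about one trial in seven, a moderate but non-significant baseline imbalance shifts the estimate by about 0.3 to 0.5 points against a planned 1.97. Both effects shrink, and can nearly vanish, if the post-treatment SD is larger than the baseline SD and r is high. The documents do not support a claim of inflated overall error or of an underpowered trial.

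**What to change.** In section 2.13, name one primary analysis: a linear model (ANCOVA) of visit 11 PSQI, or its change from visit 1, on arm, baseline PSQI and research institution, used whatever the baseline comparisons or normality checks show. Report the adjusted mean difference with its 95% confidence interval.

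Delete the baseline-significance trigger; baseline tables can remain descriptive. Keep Mann–Whitney as a sensitivity analysis only. Use the same model, each with its own baseline value, for the continuous secondary outcomes.

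The cost is a wording change in section 2.13 and in any separate analysis plan, made before the outcome data are analysed. It needs no new data and no change in sample size: baseline PSQI is already scheduled, and institution is already the stratification factor.

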## Abstract

Insomnia is a common health problem that can lead to various diseases and negatively impact quality of life. Pharmacopuncture is a new type of acupuncture that involves applying herbal medicine extracts to acupoints. Korean medicine doctors frequently use it to treat insomnia disorder. However, there is insufficient evidence to support the effectiveness and safety of pharmacopuncture for insomnia disorder. We designed a pragmatic randomized controlled trial to compare the effectiveness of pharmacopuncture and acupuncture for insomnia disorder. This multi-site, randomized, acupuncture-controlled trial will enroll 138 insomnia patients. The subjects will be randomly assigned to one of two groups, pharmacopuncture or acupuncture, at a 2:1 ratio. For 4 weeks, the participants will receive ten sessions of pharmacopuncture or acupuncture treatment and will be followed up for 4 weeks after the treatment ends. The Pittsburgh Sleep Quality Index score is the primary outcome measure. Insomnia severity index score, sleep parameters recorded using actigraphy and sleep diaries, physical symptoms associated with insomnia, emotions, quality of life, medical costs, and safety are the secondary outcome measures. The findings of this trial willprovide evidence that will be useful in clinical decision-making for insomnia treatment strategies.

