Pharmacopuncture is a new type of acupuncture therapy that involves injecting herbal medicine extracts into acupoints, thus producing a combination of mechanical and chemical effects. Its benefits include a relatively quick effect and ease of administered dosage control. Additionally, since the herbal medicine is administered and absorbed directly into the acupoints without direct involvement of the gastrointestinal tract, this treatment can be extended to patients who cannot consume herbal medicine orally [35]. Pharmacopuncture is frequently used for the treatment of insomnia, and more than one-third of Korean medicine doctors reported using this treatment for insomnia in 2016 [31]. A 2020 survey showed that the most commonly used type of pharmacopuncture for insomnia is placental pharmacopuncture, followed by Hwangryunhaedok-tang, Ouhyul, and Bufonis venenum pharmacopuncture [36]. A systematic review reported that the decrease in PSQI score after pharmacopuncture therapy was significantly greater than that after pharmacotherapy or acupuncture [37]. Korean medicine doctors theorize that pharmacopuncture may effectively and safely treat insomnia. However, the implementation of this therapy is limited in clinical settings because of insufficient clinical evidence and the high cost of procedure, which is due its exclusion from national health insurance coverage [36].

However, RCTs comparing the effectiveness and safety of pharmacopuncture and acupuncture on insomnia disorder are scarce. Furthermore, to the best of our knowledge, there have been no RCTs conducted in Korea comparing the effectiveness and safety of pharmacopuncture and acupuncture on the improvement of insomnia. 

Therefore, a well-designed RCT that can reflect the clinical status and context of Korean medicine is needed. We will perform a multi-site, pragmatic, randomized, acupuncture-controlled trial to investigate the effectiveness and safety of pharmacopuncture compared with acupuncture covered by NHI for insomnia disorder. The results of this study will provide clinical and economic evidence that will be helpful in clinical decision-making for various insomnia treatment strategies used in Korean medical clinical settings.

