#### 2.9.4. Cost Data

In this study, direct medical and non-medical costs and costs of productivity loss will be considered. Direct medical costs include expenses associated with pharmacopuncture, prescribed hypnotics, first or revisit diagnoses, and examination costs. Direct non-medical cost consists of the round-trip expenses for participating in clinical trials. The productivity loss costs will be calculated by multiplying the lost productivity scores by the hourly wage. The Work Productivity and Activity Impairment (WPAI) questionnaire will be used to calculate the lost productivity scores [54]. 

The result of the cost-effectiveness analysis will be expressed as the incremental cost-effectiveness ratio (ICER). This economic evaluation will include all types of costs and consider the quality-adjusted life-years (QALY) for effectiveness. QALY will be calculated using the EQ-5D-5L, and gross domestic product (GDP) per capita will be used as the threshold value for willingness to pay.

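### Read as written, section 2.13 would test skewed costs by ranks, which does not address the mean cost difference that the ICER in 2.9.4 rests on

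*Protocol article*

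**What the plan says.** The Abstract (Protocol article) closes its list of secondary outcomes with costs: "quality of life, medical costs, and safety are the secondary outcome measures". Section 2.13 gives the testing rule: "The independent t-test or Mann–Whitney U-test will be used for analysis, depending on the normality of data distribution". If baseline variables differ significantly between groups, "regression analysis with covariates (analysis of covariance) will be conducted" instead. It then extends the rule: "The primary and secondary outcome measures will be analyzed in the same manner". It makes no exception for costs or QALYs.

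Section 2.9.4 defines what is costed: "direct medical and non-medical costs and costs of productivity loss will be considered". It expresses the cost-effectiveness result as an ICER, with QALYs from the EQ-5D-5L and GDP per capita as the willingness-to-pay threshold. It names no test and no interval for the cost difference.

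**The concern.** An ICER divides a difference in mean cost by a difference in mean QALYs. The decision-maker needs arithmetic means because mean times number of patients is the budget. A Mann-Whitney test asks something else: whether a randomly chosen pharmacopuncture patient tends to cost more than a randomly chosen acupuncture patient. The two questions can have different answers when one arm's costs are shifted for most patients and the other arm's costs sit in a longer tail.

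The trial is meant to inform policy on a treatment that is not reimbursed. A p-value by ranks that says more costly, printed beside a mean difference that is neutral or favourable (or the reverse), would confuse that message.

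**Working it through.** **1. Which branch costs would take.** Productivity loss is a WPAI score times an hourly wage (2.9.4) in participants aged 19-80 (2.4), so some will probably have none. Hypnotic costs arise only in users. Zero-heavy, right-skewed totals are therefore plausible. The protocol names no normality test. If Shapiro-Wilk at 0.05 is assumed, it flagged non-normality in 99.9-100% of trials simulated with skewed costs. Unless baseline imbalance triggers ANCOVA, the stated rule then selects Mann-Whitney.

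**2. Why shapes may differ between arms.** The Introduction says that acupuncture is reimbursed and attributes to pharmacopuncture "the high cost of procedure, which is due its exclusion from national health insurance coverage". One arm thus carries an extra fee for every patient. Any benefit on productivity would act only on those who have a loss.

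**3. Ranks against means, in closed form.** The plan states no figure for costs, so there is none to reproduce. Assume log-normal costs with mean m and log-SD s, where T is pharmacopuncture and C is acupuncture:

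- Median = m × exp(−s²/2).
- P(T>C) = Φ{[ln(mT/mC) − (sT² − sC²)/2] / √(sT² + sC²)}.
- Equal means of 100, s = 0.5 v 1.0: medians 88.2 and 60.7; P(T>C) = Φ(0.375/1.118) = Φ(0.335) = 0.631.
- Pharmacopuncture mean 90 against 100, same s: P(T>C) = Φ((−0.105 + 0.375)/1.118) = Φ(0.241) = 0.595.

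Mann-Whitney is referred to P(T>C) = 0.5, so it has power against both cases. Yet the mean difference is nil in the first and favours pharmacopuncture in the second.

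**4. Simulation: fee offset by productivity.** Sizes are from section 2.3 (92 v 46 enrolled, 74 v 37 evaluable), two-sided 5%. The assumptions, in arbitrary units, are:

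- other costs 100 (SD 20);
- acupuncture productivity loss with mean 100, log-normal, CV 1 to 1.5, zero in 0% or 50% of patients;
- pharmacopuncture fee of +10, +20 or +30, with mean productivity loss lower by the same amount, so mean costs are equal.

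Results at 92 v 46 with equal means:

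| Fee | Mann-Whitney rejects |
|---|---|
| +10 | about 7-15% |
| +20 | about 12-39% |
| +30 | about 20-63% |

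A repeat run gave 6-64% over all settings, with Welch t at 4-9%. At 74 v 37 and fee +30, Mann-Whitney rejected in 17-55%. With fee +30, half at zero loss and pharmacopuncture truly cheaper by 10, Mann-Whitney called it significantly dearer in 39-58%.

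**5. Other assumed shapes.** The table gives the share of trials calling pharmacopuncture significantly dearer, at 74 v 37 and then 92 v 46.

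| Scenario | Mann-Whitney | Mean-based |
|---|---|---|
| Log-normal, equal means, s 0.5 v 1.0 | 59%, 68% | Welch 9%, 8% |
| Same s, means 90 v 100 | 38%, 44% | Welch 3%, 3% |
| Fee 20 for all; cost of 200 in 5% v 15%; means 20+40+10 = 70 v 40+30 = 70 | 85%, 90% | bootstrap 5%, 5% |
| As above with fee 15; means 65 v 70 | 59%, 69% | bootstrap 2%, 2% |
| Log-normal, equal means, same s (1.0 each) | 2.4%, 2.3% | no distortion |
| Log-normal, equal means, s 1.0 v 0.5 | about 0% | Welch about 1% |

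In the last row Mann-Whitney still rejects in 63% and 73% of trials, but in the direction of pharmacopuncture being cheaper. In the two fee-plus-rare-high-cost scenarios, 25-39% of trials had Mann-Whitney calling pharmacopuncture dearer while its observed mean cost was equal or lower. In those trials the test and the ICER numerator pointed opposite ways in the same data.

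**The case against.** **The routing is inferred.** Section 2.9.2 does not list costs. They have their own section with their own result, and 2.13 never mentions costs, QALYs or the ICER. The secondary label comes only from the Abstract. This stands as a limit, but no sentence takes costs out of the 2.13 rule.

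**Safety is on the same Abstract list and plainly is not analysed by t-test or Mann-Whitney.** True, but 2.9.6 gives safety its own comparison, of AE incidence. Section 2.9.4 gives the cost difference none.

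**What is missing may belong to a full analysis plan.** Bootstrap detail may well be left there, and its absence is not the point. The point is a stated rule that, read as written, covers costs and fits them badly.

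**Read narrowly, medical costs leave out productivity loss.** Ten sessions are planned in each arm, and the listed direct medical items show little that could offset a fee. A mainly additive fee moves means and ranks the same way. This stands: on that reading a reversal is unlikely. But the ICER in 2.9.4 uses all cost types.

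**The scenarios are invented.** Also true. No section predicts that productivity gains will offset the fee, and no cost distribution is given. A reader might infer that this trial should be expected to label pharmacopuncture falsely dearer. The documents do not support that: equal shapes give no error, and reversed skew changes its direction.

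**Conclusion.** The point holds in a limited form. As written, the only between-group test that the article provides for a secondary outcome called medical costs would, for skewed data, be a rank test that does not test the ICER numerator. When the arms' cost distributions differ in shape, its p-value can disagree with the ICER either way. The 6-64% range for Mann-Whitney, against 4-9% for Welch, shows how large this can be under the assumed fee-offset model. It is not a forecast for this trial.

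A reader might also infer that the ICER would be wrong or built on ranks. Nothing says so: the ICER would presumably still use means, and only the p-value beside it would be at fault. If baseline imbalance triggers ANCOVA, means are compared anyway, although the cost estimand would then depend on baseline tests and a normality check.

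Severity is minor to moderate. Only the secondary economic outcome is affected, and the PSQI comparison is untouched.

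**What to change.** In 2.13, exempt costs and QALYs from the rule that picks the test by normality. Suggested wording: Costs and QALYs will be compared as arithmetic means, whatever their distribution, using a nonparametric bootstrap that resamples each participant's cost and QALY together within arm. The 95% interval for the mean cost difference, and the uncertainty of the cost-effectiveness result at the GDP-per-capita threshold, will be taken from the same bootstrap. No rank test will be used for costs.

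The cost is one paragraph of text and a short script, with no new data or participants. The downside is that the interval for a mean difference in skewed costs may be wide.

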### 2.12. Criteria for Discontinuation and Withdrawal

Treatment will be discontinued and participation will be withdrawn according to the following criteria: (1) Request for discontinuation or withdrawal of consent by participants or their legal representative; (2) diagnosis of any medical condition that makes the participant ineligible for this trial; (3) incidence of any serious AEs; (4) violation of the study protocol; (5) changes in dosage or type of sleeping pills already used during the trial period (from screening test to post intervention); (6) loss to follow-up; (7) use of any medications or undergoing therapies that will affect the study results without the permission of investigators; (8) more than three consecutive absences from intervention or participation in less than seven sessions of the intervention; and (9) other conditions wherein participation is judged to be inappropriate by the investigator in charge.

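### Safety is analysed in the effectiveness FAS, which drops ineligible participants even after treatment; a separate all-treated safety set is needed

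*Protocol article*

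**What the plan says.** Section 2.13 names one primary population for both purposes: "The FAS is the primary analysis of effectiveness and safety". It defines that set as follows: "It will include all participants initially assigned to each group, except those who did not meet the eligibility criteria". Two further exclusions come after this: "those who had not received any intervention" and "those who had not completed any outcome measurements". The only other set is narrower: "The per-protocol analysis will include participants who have completed more than seven sessions".

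Section 2.9.6 collects AEs at each visit. It plans counts and percentages of participants with AEs or laboratory abnormalities in each group, and a between-group comparison of incidence, but it names no population for them. Section 2.3 explains that the 2:1 ratio was chosen "in order to obtain data on the side effects (safety) of the pharmacopuncture while securing statistical power". Section 2.12 lists among its reasons for withdrawal "incidence of any serious AEs", and also a diagnosis that makes the participant ineligible.

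**The concern.** Exclusions that may be defensible for an effectiveness analysis do not suit a safety analysis. A person who has had a session has been exposed, and whether they should have been enrolled, or later filled in a questionnaire, does not change that. The entry criteria in Section 2.5 screen out, among others, people with abnormal liver or kidney tests, serious chronic disease, uncontrolled hypertension or pregnancy. Someone enrolled in error under one of these and then treated belongs in the harms data, and Section 2.13 as worded takes them out of both numerator and denominator.

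At stake is the AE rate in the pharmacopuncture arm, which the unequal allocation was partly meant to inform. The article does not leave the safety population to a later document. It states one, and the one it states carries effectiveness exclusions.

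**Working it through.** The plan gives no AE rate to reproduce, so the check is mainly a reading of the sections together.

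**Step 1: which set supplies the safety denominator?** Section 2.9.6 gives none and Section 2.13 gives the FAS. The per-protocol set is narrower, so it cannot restore anyone whom the FAS drops. No all-treated set appears.

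**Step 2: which FAS exclusions can remove a treated participant?**

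| FAS exclusion (Section 2.13) | Can it remove someone already treated? |
|---|---|
| Received no intervention | No; harmless for safety |
| Did not meet eligibility criteria | Yes; no exception is stated for treated participants |
| No outcome measurement completed | Depends on what counts as an outcome measurement |

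**Step 3: the third exclusion under each reading.**
- *Only post-baseline PSQI, ISI or VAS scores count.* Table 1 places the first of these at visit 6. Section 2.6 has outcomes assessed before treatment, so sessions 1 to 5 (visits 1 to 5) are complete by then. A participant withdrawn for a serious AE in that window would leave the FAS.
- *Any outcome counts.* Table 1 has PSQI, ISI and VAS at visit 1, sleep diary and actigraphy from screening and at visits 2 to 5, and AE checks from visit 1. The abstract lists safety among the secondary outcomes. Few or no treated participants would then be lost.

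The text does not choose between these readings.

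**Step 4: how much could it matter?** Let N be the number treated in an arm, k the number of them whom the FAS excludes, r the AE rate among those kept and q the AE rate among those excluded. Then

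all-treated rate = [(N − k)·r + k·q] / N, so all-treated rate − FAS rate = k·(q − r)/N.

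The sign depends on whether q is above or below r, and the document gives neither, nor k. Since q − r lies between −1 and 1, each excluded participant shifts the rate by at most 1/N. With the planned arms of Section 2.3, and assuming that all are treated, this is 1/92 = 1.1 percentage points for pharmacopuncture and 1/46 = 2.2 points for acupuncture.

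For scale only, take N = 92 and an *assumed* r = 10%, so that the FAS reports 10.0%. The all-treated rate would be:

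| k (assumed) | q = 0% | q = 50% | q = 100% |
|---|---|---|---|
| 2 | 9.8% | 10.9% | 12.0% |
| 5 | 9.5% | 12.2% | 14.9% |

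Example: k = 5, q = 50% gives 10% + 5 × (0.50 − 0.10)/92 = 10% + 2.2% = 12.2%. These figures show sensitivity and are not an estimate for this trial.

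**The case against.** The strongest reply is that very few treated participants would be affected. Eligibility, including laboratory tests and ECG, is checked at screening a week before allocation, so errors of enrolment should be uncommon. The eligibility exclusion reads most naturally as referring to entry criteria. A disqualifying diagnosis made during treatment is a withdrawal reason in Section 2.12, and the article does not say that it also removes the person from the FAS. Section 2.9.6 says that all reported AEs are collected, and Section 2.11 provides separate monitoring of laboratory and AE data, so early harms would not go unseen. All of this stands and limits the likely size. It does not change the rule: collecting and monitoring AEs does not set the denominator of the reported rates, and Section 2.13 does.

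A reader might go further and infer that the plan loses people because they were harmed early, and so understates AE rates. The documents do not support that. It requires the post-baseline reading of the third exclusion, which Section 2.13 does not state. Visit 6 is the first on-treatment time only for PSQI, ISI and VAS; diary and actigraphy are scheduled throughout.

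It may also be said that the unseen analysis plan could define a safety set. If it does, it conflicts with this article's explicit statement, and the two need to be reconciled.

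**Conclusion.** The point holds for treated participants found not to have met the eligibility criteria: Section 2.13, followed as written, removes them from the primary safety analysis. This needs no assumption beyond the text. For participants who leave before visit 6 the text is ambiguous, and the loss occurs only under the narrower of two possible readings.

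The size and direction of any bias cannot be derived from the document. The bound of 1.1 points (pharmacopuncture) or 2.2 points (acupuncture) per excluded participant assumes that the planned 92 and 46 are all treated. This is a badly fixed rule that is worth correcting before the data are analysed. It is not evidence that the AE rates will be materially wrong.

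The FAS also groups participants as assigned. Grouping by treatment received is the better choice for harms, but nothing in the article suggests that crossing between arms is expected, so this is secondary.

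**What to change.** In Section 2.13, restrict the FAS to effectiveness. Add a safety set of all participants who received at least one session, grouped by treatment received, regardless of later eligibility findings or completion of outcome measurements. Name this set in Section 2.9.6 as the population for the AE and laboratory summaries and for the between-group comparison of incidence.

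For the effectiveness FAS, state whether a baseline measurement alone satisfies the outcome-measurement condition.

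The cost is a few sentences in the protocol and the matching text in the analysis plan. AEs are already recorded at every visit, so no new data are needed. The change should be made before outcome and AE data are examined by group, because a safety denominator chosen afterwards would be hard to defend.
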